### Data collection, quality and procedures

All data collected during study visits and telephone calls with each patient will be recorded in the CLEAR source documents/electronic case report form (CRF). If a participant withdraws during their first year on the study, they will be asked to attend follow-up visits for collection of outcome data. If they do not wish to attend outcome data collection, permission will be sought to access medical notes for collection of data relevant to the trial e.g. the use of antibiotics. If a participant withdraws from all parts of the study, their anonymised data (recorded up to the point of withdrawal) will be included in the study analysis. All patient data will be anonymised.

### Data management

Trial data will be entered onto the electronic case report form (CRF) on a clinical trial database (MACRO) by delegated site personnel and processed electronically as per the Northern Ireland Clinical Trial Unit’s (NICTU) standard operating procedures (SOPs) and the study-specific data management plan (DMP). Data queries will be “raised” electronically using MACRO where clarification from site staff is required for data validations or missing data. Site staff will respond electronically to data queries, ensuring that necessary amendments are made to the clinical trial database.

### Statistical analysis

Baseline characteristics, follow-up measurements and safety data will be described using descriptive summary measures depending on the scale of measurement. The primary analysis will be conducted on a modified intention-to-treat basis consisting of randomised participants with data from at least one post-baseline efficacy assessment. A per-protocol analysis may also be conducted to compare treatment groups. Groups will be compared for the primary outcome (number of exacerbations over 52 weeks) and antibiotic use (number of days of antibiotic use over 52 weeks) using negative binomial regression adjusted for baseline characteristics and other covariates. The QoL-B and other continuous outcomes will be compared between groups using analysis of covariance (ANCOVA) adjusting for baseline characteristics and other covariates. The trial’s 2 × 2 factorial design permits the separate testing of the effects of HTS and carbocisteine on HRQoL and the detection of any interaction between them. These tests will be implemented using three contrasts (representing HTS, carbocisteine and the interaction) in the models. For time to next exacerbation, Kaplan-Meier curves will be prepared and the log-rank test applied to compare the groups. Analyses will be two-sided and tested at an a priori significance level of *p* = 0.05. The primary time point has been defined as 52 weeks after randomisation. There is no adjustment for multiple testing at the different time points, because the primary outcome has been pre-defined and prioritised. Standard approaches will be used to detect missing data.

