### Treatment discontinuation

All patients allocated to a treatment group including HTS 6% will complete a drug response assessment prior to commencing HTS in accordance with a study-specific guideline and if they do not pass this they will not continue on the study. Participants may withdraw from treatment at any time, without providing an explanation, or if discontinuation is considered by the medical team to be in the best interests of the patient. Anticipated reasons for withdrawal include intercurrent significant illness, occurrence of intolerable side effects, patient request, protocol violations or decision that the study drug should be discontinued on safety grounds. A participant may be withdrawn from the study at the discretion of the Investigator due to safety concerns.

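### The primary analysis set requires a post-baseline efficacy assessment, a condition the exacerbation count does not need and which, read as a visit assessment, conflicts with the data-collection section

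*Protocol article*

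**What the plan says.** The Statistical analysis section defines the primary analysis on a "modified intention-to-treat basis consisting of randomised participants with data from at least one post-baseline efficacy assessment". The only other set it names is an optional per-protocol set. It compares exacerbation counts and antibiotic days by negative binomial regression.

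The section Data collection, quality and procedures covers people who withdraw:

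- **First step:** "If a participant withdraws during their first year on the study, they will be asked to attend follow-up visits for collection of outcome data".
- **Fallback:** "If they do not wish to attend outcome data collection, permission will be sought to access medical notes", with antibiotic use given as an example of what would be collected.
- **Withdrawal from all parts of the study:** "their anonymised data (recorded up to the point of withdrawal) will be included in the study analysis".

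The primary outcome (Outcomes) is counted over the 52 weeks after randomisation. Under Exacerbation management, patients with symptoms call the study team. Under the RSSQ heading, modified questionnaires record possible exacerbations reported between visits. The trial is open label for patients, investigators and outcome assessors (Randomisation and blinding).

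**The concern.** A rule that admits people to the primary set according to what happens after randomisation gives up part of the protection of randomisation. It is usual for an outcome that exists only if someone attends and is measured. An exacerbation count is different: it accrues from day one, and the protocol has arranged to collect it without a visit. Someone who telephones with an exacerbation and then leaves before any visit has both an event and time at risk. Someone who declines visits but allows access to notes may have a full year of outcome data.

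Allocation is known to everyone, and the Treatment discontinuation section expects some withdrawals for side effects and at the patient's request. Early loss could therefore differ between groups. If the people lost also differ in exacerbation rate, the comparison of those who remain is biased. The 15% dropout allowance replaces numbers but does not correct selection.

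**Working it through.** **The two sections side by side.** The analysis section asks for data from a post-baseline efficacy assessment and does not say whether a call or a notes extract is one.

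- *Broad reading (calls and notes count):* the two sections agree, and only people with no post-baseline data at all are left out.
- *Narrow reading (a visit is needed):* people with call or notes data only are left out, although the data-collection section says their data will be collected or included.

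**The plan's own figures.** The Sample size section gives a control mean of 0.7, SD 0.9, difference 0.4, 90% power and 5% significance; the Statistical analysis section makes the tests two-sided. A two-sample t-test calculation gives 107.36, so 108 per group and 216 in total, as stated. Then 216 × 1.5 = 324, as stated, and 324 / 0.85 = 381.2 against the stated 380. The sample size is not in dispute. At the margins, 324 / 2 = 162 per side.

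**Illustration of bias.** The document gives no early-loss rate, so the exclusion rates below are assumptions. Assume also no true effect, a mean of 0.7 in every group, and excluded patients with twice that mean (1.4). If a fraction p is excluded, the mean of those retained is (0.7 − 1.4p) / (1 − p).

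| Excluded, HTS v no HTS | Retained means | Spurious difference | Share of 0.4 |
|---|---|---|---|
| 4% v 1% | 0.644/0.96 = 0.671; 0.686/0.99 = 0.693 | 0.022 | 6% |
| 10% v 2% | 0.560/0.90 = 0.622; 0.672/0.98 = 0.686 | 0.063 | 16% |

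With SE = 0.9 × √(2/162) = 0.100 and a normal approximation, the two-sided type I error is about 5.6% in the first row and 9.7% in the second. If the excluded patients have the same mean as the rest (0.7), the bias is zero. If they are milder, say 0.35, the 10% v 2% case gives 0.665/0.90 = 0.739 v 0.693/0.98 = 0.707, a difference of 0.032 in the opposite direction.

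**What a wider analysis set would recover.** Suppose leavers stay in with their observed time only, t = weeks/52. The group rate is then [(0.7 − 1.4p) + 1.4pt] / [(1 − p) + pt]. Visit 3 is at 8 weeks (Intervention and comparator), so a first post-baseline visit should come no later than that; weeks 2 and 8 are taken as examples.

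| Case | Leavers excluded | Kept, leave at week 2 | Kept, leave at week 8 |
|---|---|---|---|
| 10% v 2% | 0.063 | 0.6863 − 0.6255 = 0.061 | 0.6879 − 0.6353 = 0.053 |
| 4% v 1% | 0.022 | 0.6932 − 0.6720 = 0.021 | 0.6940 − 0.6755 = 0.019 |

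In the 10% v 2% case, 96% (week 2) or 83% (week 8) of the bias remains; the 4% v 1% case is similar. If instead every early leaver allowed notes access for the full year, the mean is restored: 0.9 × 0.622 + 0.1 × 1.4 = 0.70, and likewise in the other group, so the bias is removed.

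**The case against.** Four objections have force.

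1. A reader might infer that stopping the allocated treatment early decides who is analysed. The document does not support this. People who withdraw are asked to keep attending, notes are sought if they decline, and data up to withdrawal are kept. This objection stands in full.
2. A reader might infer that people with only call or notes data are definitely excluded. The rule does not mention visits, so this is one reading and not a stated exclusion. It can also be said that the meaning of an efficacy assessment belongs in the analysis plan, which is to be finalised before analysis. That is fair for the definition of the term. It does not remove the point, because the article itself fixes a conditional primary set and names no all-randomised analysis.
3. The exclusion rates are invented. A 10% loss before any assessment is large beside a planned 15% dropout for the whole trial, and the direction can reverse. This stands.
4. For people who withdraw completely, changing the set hardly changes the answer, as the second table shows. This also stands: for them it is a missing-data problem.

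The drug response assessment in the HTS groups is a separate matter. The Treatment discontinuation section says of those patients that "if they do not pass this they will not continue on the study". It does not say whether they are still followed for outcomes, so it is not used in the figures here.

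**Conclusion.** The point holds in a limited form. The primary set carries a post-randomisation condition that the exacerbation count does not need, and on a visit-based reading it contradicts the data-collection section. Those affected are early leavers with only call or notes data (on that reading) and those with no post-baseline data. The document supports no estimate of how many there will be or which way any bias would run. The illustrative differences of 0.022 and 0.063 rest wholly on the assumed exclusion rates and on a doubled exacerbation rate among those excluded; they are small against 0.4 and vanish if leavers are typical. The main gain from changing the set is for participants with call or notes data. The change is still worth making because it costs almost nothing and settles the choice before outcomes are seen in an open-label trial.

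**What to change.** - For exacerbation count, time to next exacerbation and antibiotic days, define the primary set as all randomised participants in their allocated group, each contributing observed time from randomisation. Use log follow-up time as the offset in the negative binomial model.
- State that call and notes data count.
- Keep the post-baseline condition only for outcomes that need a visit measurement: QoL-B, SGRQ and lung function.
- Align the Statistical analysis section with the section Data collection, quality and procedures. Reconcile both with Treatment discontinuation on whether patients who do not pass the drug response assessment are followed and analysed.
- Add a sensitivity analysis for participants who leave early with little or no follow-up, varying their assumed exacerbation rate by group, since the change of set alone does little for full withdrawers.

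The cost is wording and slightly more analysis work, with a few participants contributing short follow-up. The sample size of 380 stands.

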### Objectives

The primary objective of the CLEAR trial is to determine whether HTS (6%) and/or carbocisteine reduces the mean number of exacerbations over 52 weeks. Secondary objectives are to determine whether HTS and/or carbocisteine improve disease-specific HRQoL, reduce time to next exacerbation, reduce number of days of antibiotics for treatment of exacerbations, improve generic HRQoL, are acceptable from a patient satisfaction perspective, are associated with adverse events (AEs) and improve lung function over 52 weeks. The study will also assess cost effectiveness and treatment adherence.

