### Outcomes

The primary outcome measure is the mean number of exacerbations over 52 weeks after randomisation. Secondary outcome measures are disease-specific HRQoL (respiratory symptoms of the domain of Quality of Life - Bronchiectasis (QoL-B) [29]), time to next exacerbation, number of days of antibiotics related to exacerbations, generic HRQoL (Euroqol 5 dimensions 5 levels (EQ-5D-5 L) [30]), measurement of health impairment using the St Georges Respiratory Questionnaire (SGRQ) [2]), health service use, quality-adjusted life years (QALYs), patient preferences for treatment, adverse events, lung function and adherence to trial treatment over 52 weeks.

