### Randomisation and blinding

Treatment allocation at each site will be assigned using a concealed automated randomisation process provided by an external organisation. Participants who give their consent will be allocated using a fixed block size to one of the four groups (three intervention groups or one standard care group) in a 1:1:1:1 ratio using a central randomisation system. Randomisation will be stratified by (1) site, (2) exacerbations in the last year (2–3 times, > 3 times) (to minimise baseline imbalances in antibiotic use) and (3) current use of macrolides (yes, no). The trial is open label, and patients, investigators and outcome assessors will be aware of treatment allocation.

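### Time to next exacerbation is given only a log-rank test between undefined groups, with no per-drug effect estimate and no use of the randomisation strata

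*Protocol article*

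**What the plan says.** In the protocol article, the Outcomes section lists this endpoint among the secondary measures ("time to next exacerbation, number of days of antibiotics related to exacerbations"). The Objectives ask whether HTS and/or carbocisteine "reduce time to next exacerbation", so the question is put for each drug.

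Under Statistical analysis, exacerbation counts and antibiotic days are compared "using negative binomial regression adjusted for baseline characteristics and other covariates", and continuous outcomes by ANCOVA with similar adjustment. The factorial design is then said to be one that "permits the separate testing of the effects of HTS and carbocisteine on HRQoL and the detection of any interaction between them", and "These tests will be implemented using three contrasts (representing HTS, carbocisteine and the interaction) in the models". The next sentence deals with time to next exacerbation: "Kaplan-Meier curves will be prepared and the log-rank test applied to compare the groups". Nothing further is said about this outcome, except that the general rule applies: "Analyses will be two-sided and tested at an a priori significance level of" 0.05.

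Under Randomisation and blinding, "Randomisation will be stratified by (1) site, (2) exacerbations in the last year" (2–3 or more than 3), and (3) current macrolide use. The Sample size section claims 98% power for a 75% longer median time to exacerbation. The Health economics evaluation section announces a detailed statistical analysis plan, which is not at hand.

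**The concern.** The named method does not deliver what the objective asks for. A log-rank test gives a p-value without an effect size or interval. The three factorial contrasts are placed in regression models, and the sentence that introduces them mentions HRQoL only. A log-rank test is not one of those models, so this is the one efficacy outcome with a named method in that section that has no stated route to an HTS, carbocisteine or interaction estimate. It is also the one for which no adjustment is mentioned, although randomisation was stratified.

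The comparison itself is not fixed either, because the groups are not defined. If the four arms are compared, a significant result shows only that some arm differs, and an effect of one drug is spread over three degrees of freedom. If the two margins are compared, each drug is tested directly. The choice should be settled before the data are seen.

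A separate slip is that the Objectives present a shorter time to next exacerbation as the benefit, while the Sample size section powers for a longer one.

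**Working it through.** **Inputs.** From the Sample size section: 75% increase in median time, 98% power, control mean 0.7 exacerbations over 52 weeks, SD 0.9, 324 patients before dropout and 380 in total. From Statistical analysis: two-sided 5%. Assumption: exponential times, so HR = 1/1.75 = 0.571 and ln(1.75)² = 0.5596² = 0.3132.

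**1. The stated 98%.** For a two-group, 1-df log-rank test with equal groups (Schoenfeld), events = 4 × (1.960 + 2.054)² / 0.3132 = 206. The Freedman formula gives 217. The article states neither an event count nor a control median, so the 98% cannot be fully reproduced. As a two-group figure it implies about 206 events.

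**2. Events implied by the article's own control mean.** Poisson: 1 − exp(−0.7) = 0.503 of controls and 1 − exp(−0.7 × 0.571) = 0.330 of treated patients have an event. Then 324 × (0.503 + 0.330)/2 ≈ 135 events. Negative binomial with k = (0.81 − 0.7)/0.49 = 0.224 gives 0.478 and 0.318, hence 129 events. A control rate of about 1.5 a year gives 206 to 219 events in 324 patients.

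**3. Four arms against a factorial margin.** With one drug active and no interaction, both tests have noncentrality λ = events × 0.3132 / 4. Power is the probability that a noncentral chi-square exceeds 3.84 (1 df) or 7.81 (3 df).

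| Events | Basis | λ | Per drug, 1 df | Four arms, 3 df | Loss (points) |
|---|---|---|---|---|---|
| 206 | implied by the 98% | 16.1 | 98.0% | 93.6% | 4.4 |
| 158 | 380 patients, rate 0.7, Poisson | 12.4 | 94.1% | 85.3% | 8.8 |
| 135 | 324 patients, rate 0.7, Poisson | 10.6 | 90.2% | 78.6% | 11.6 |
| 129 | 324 patients, rate 0.7, negative binomial | 10.1 | 88.8% | 76.6% | 12.2 |

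**4. What a significant result would mean.** In a simulation of 2,000 trials of 324 patients (control rate 0.7, stratum HR 2, only the other drug active), the four-arm test rejected in 77% of trials. The test of the inactive drug on its margin rejected in about 5%.

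**5. Strata.** The same simulation was run with a prognostic exacerbation-history stratum split 50:50. Macrolide use was set at 30% with no effect, and site was not modelled; all of these are assumptions. The table shows power of the per-drug test at control rate 0.7 with one drug active.

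| Stratum HR | Unstratified | Stratified |
|---|---|---|
| 1 | 89.8% | 89.3% |
| 2 | 87.8% | 89.7% |
| 3 | 86.9% | 91.1% |

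With both drugs active, the gain at stratum HR 3 is from 79.2% to 84.0%. The gain is therefore about 0 to 5 points.

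**The case against.** A reader might infer that the plan fixes a 3-df test of four arms and so discards the factorial design. The documents do not support that as fact. The article does speak of four groups when it describes the design, but the Statistical analysis section also uses the word groups for the count and continuous outcomes before adding the factorial contrasts. The 216-patient calculation is a two-group one, and the 98% also fits a two-group test: at 206 events a four-arm test would have 93.6%. A log-rank test on each margin is therefore quite possible, and on that reading the 3-df loss disappears.

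Nor is a loss of power certain under the four-arm reading. If both drugs work equally, the four-arm test rejects its global null more often (94%, against 82% for one drug's test at control rate 0.7), though it answers a different question. The 12-point loss rests on an event count that the article does not give; at the count implied by its own 98%, the loss is about 4 points.

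On strata, an unstratified log-rank test remains valid after stratified randomisation. The article gives balance in antibiotic use, not prognosis, as the reason for the exacerbation stratum. Strata, intervals and the handling of site are commonly left to the analysis plan, and the article states no interval for any outcome.

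These points limit the size of the finding but do not remove it. The article names a test, and that test gives no estimate for either drug on either reading of the groups. The comparison is left open, and nothing links the test to the contrasts.

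**Conclusion.** The concern holds in limited form. The named analysis of this secondary outcome does not estimate the effect of either drug, names none of the randomisation strata, and leaves open whether arms or margins are compared.

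The power cost is conditional. It is about 4 to 12 points if the four arms are compared, one drug is active at HR 0.571 and times are exponential. It is nil if the margins are compared. Omitting the strata costs about 0 to 5 points for assumed stratum hazard ratios of 1 to 3.

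A reader might also infer that the 98% is wrong, because a control rate of 0.7 gives about 90% in 324 patients. The article does not support that conclusion: it states no event count, and a control rate of about 1.5 a year would give 98%.

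The primary conclusion is not at risk, since it rests on the adjusted negative binomial model. This is an inexpensive improvement that should be made. The word reduce in the Objectives is a plain wording error, with no effect on a two-sided test.

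**What to change.** - State that time to next exacerbation is compared for each drug on its factorial margin, using a Cox model with HTS and carbocisteine as factors, stratified by prior exacerbations (2–3, more than 3) and macrolide use and allowing for site.
- Report each drug's hazard ratio with its 95% CI, and the interaction from a second model.
- If a log-rank p-value is wanted, give one per drug, stratified by the other drug and by these strata.
- Keep the Kaplan-Meier curves, by drug and by arm.
- Give the event count behind the 98%.
- Change the objective to increase time to next exacerbation, in agreement with the Sample size section.

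The cost is wording in an analysis plan that the article says is still to be finalised. The randomisation variables are already collected. The Cox model brings a proportional-hazards assumption, which needs a routine check. With at least 16 sites, site is better handled by a random effect or robust variance than as a further stratum: 16 × 2 × 2 = 64 strata would hold about five of 324 patients each.

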### Health economics evaluation

A within-trial economic evaluation will assess the cost-effectiveness of the four treatment options at 26 and 52 weeks from the perspective of the NHS and Personal Social Services. A within-the-table analysis will be performed, treating the four groups in the factorial design as mutually exclusive treatments. Economic outcomes will then be estimated and presented separately for each treatment option so that the effect of any interactions can be seen directly. We will estimate the cost per QALY gained, the cost per exacerbation avoided and the net benefit (NB) in each of the treatment groups. Regression analysis with an interaction term will be performed, as a robustness check and to control for baseline covariates. Participants’ health service use and prescriptions (both related and unrelated to their BE) will be prospectively collected from baseline to 52 weeks using logs and questionnaires administered as per Table 1. Costs will be calculated by attaching appropriate unit costs from national sources. QALYs will be calculated using responses on the EQ-5D-5 L over the study period. Uncertainty surrounding the incremental cost-effectiveness ratios will be summarised in cost-effectiveness acceptability curves showing the probability of the therapeutic strategies being cost effective at different threshold levels of willingness to pay per QALY and per exacerbation avoided. Sensitivity will be analysed to explore the impact on cost effectiveness of variations in key parameters. Detailed statistical and health economic analysis plans will be finalised before the commencement of analysis.

